**4.2 Immunogenicity assessments**

*4.2.1 Antibody responses*

Detection of binding antibodies to HIV proteins covering the vaccines will be assessed using ELISA.

Optional assay

Analysis of neutralizing antibodies to HIV subtypes A, B, C and E in case of existing binding antibodies.

*4.2.2 Cellular responses*

The following HIV-1-specific cellular immune responses will be determined:

- Primarily, IFN-у ELISPOT responses using fresh PBMC including determination of cross-clade responses, using pools of overlapping peptides representing the immunogens.
- 8-colour intracellular cytokine staining (ICS) using fresh PBMCs and conducted against the same peptide pools as in the ELISPOT and testing both for CD8 and CD4 T cell responses.
- Multicolour ICS staining for measuring polyfunctional responses using cryopreserved PBMC, including cytokines/chemokines, markers for cytolytic capacity and immunphenotyping of responding cells.
- Mapping of novel epitopes recognised by vaccinees using matrices of peptides in ELISPOT.
- Lymphocyte proliferation assay (LPA) to immunizing antigens using fresh PBMC and a standard 3H-thymidine uptake assay and /or a flow cytometry based assay (CFSE or FASCIA).

Optional assay

- Viral inhibition assay
- Cellular reactivity against vaccinia antigens

*4.2.3 HLA analysis and immune reactivity gene sequences*

HLA typing will be performed by molecular methods at one time point. Analyses of immune reactivity gene sequences will optionally be performed. DNA is extracted by validated methodology from peripheral lymphocytes according to protocol. The DNA is stored at -20ºC under single code labelling and typed. The HLA type will be determined to oligo-allelic level by sequencing for classes I and II (HLA-A, -B, -C, DQ, -DR, -DPA1 and -DP1). Typing will then be performed by sequence-specific primers SSP-PCR (Olerup, GenoVision). HLA class I restricted alleles will be matched to epitopes giving rise to known or novel identified epitopes by a peptide-matrix analysis. The strength or increased strength of immune reactions (see above) will be compared to initial reactivities and to those of individuals receiving different doses of HIV DNA vaccine or receiving HIV MVA-CMDR. For class II reactivities the comparisons will be made to development of both antibody and CD4+ antigen-specific reactivity. Clinical sensitivity is related to the strength of immune reactivity by electroporation delivery compared to mode of vaccine delivery. The immunological response in each individual can be related to the changes of his/her own reactivities over time. The patient can participate in the study without the HLA typing.

**4.3 Other assessments**

*4.3.1 Antibodies against Vaccinia*

Serum samples will be stored for analysis of binding and neutralizing antibodies to vaccinia.

*4.3.2 Analysis of peptide reactivity (optionally)*

Cellular samples for analysis of peptide reactivity compared to preclinical animal reactivities after electroporation (preferably 3-4 times during the study).

*4.3.3 Analysis of anti-DNA reactivity (optionally)*

- Extended analysis of DNA antibodies.
- Cellular samples for analysis of anti-DNA reactivity.

*4.3.4 Punch biopsy (optionally)*

The presence of DNA vaccine plasmids will be determined in a punch biopsy. Histopathology and an attempt to estimate HIV gene presence and expression will be made.

*4.3.5 Genital infection*

The assays will be conducted at the SWEDAQ certified Labmedicin Huddinge University Hospital laboratories if clinically indicated.

*4.3.6 Following adverse event*

Other assessments may be performed as clinically indicated due to an adverse event.

*4.3.7 Concomitant medication*

Participants will be asked about medication taken at each visit up to and including week 60, and this will be recorded in the case record form. Thereafter, they will be asked about medication only in relation to adverse events reported. It is expected that the name of the drug, indication for use, dose, frequency, start and stop dates will be available for prescription-only medication, either from the participant or from the prescribing physician. For medication available over the counter, the maximum information available on questioning the participant will be recorded.

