**1.2 Design**

The trial is randomised and placebo controlled.

Study Design

| **Group** | **N** | **Mode of Immunization**  **(w 0, 6 , 12)** | **Mode of delivery** | **Left arm (Ampoules 1**  **env)** | | **Right arm (Ampoules 2**  **gag, Rtmut)** | **Boost immunization**  **(w 36 and 60)** |
| --- | --- | --- | --- | --- | --- | --- | --- |
| B1 | 10 | Id  ZetaJet® | No electroporation | 1 inj 100µl  0,3 mg DNA* | 1 inj100µl  0,3 mg DNA* | | 1 im inj needle  MVA 108 pfu |
|  | 2 | Id  ZetaJet® | No electroporation | 1 inj 100µl saline | 1 inj 100µl saline | | 1 im inj needle  100µl saline |
| B2 | 10 | Id  ZetaJet® | electroporation | 1 inj 100µl  0,3 mg DNA* | 1 inj 100µl  0,3 mg DNA* | | 1 im inj needle  MVA 108 pfu |
|  | 2 | Id  ZetaJet® | electroporation | 1 inj 100µl saline | 1 inj 100µl saline | | 1 im inj needle  100µl saline |
| B3 | 10 | Id  ZetaJet® | electroporation | 1 inj 100µl  0,3 mg DNA* | 1 inj 100µl  0,3 mg DNA* | | 2 id inj Zetajet®,  tot. 0,6 mg DNA + electroporation |
|  | 2 | Id  ZetaJet® | electroporation | 1 inj100µl saline | 1 inj100µl saline | | 2 id inj Zetajet®,  tot 200µl saline +  electroporation |
| B4 | 10 | Id  ZetaJet® | electroporation | 1 inj100µl  0,3 mg DNA** mixed ampoules | 1 inj100µl  0,3 mg DNA** mixed ampoules | | 1 im inj needle  MVA 108 pfu |
|  | 2 | Id  ZetaJet® | electroporation | 1 inj100µl saline | 1 inj100µl saline | | 1 im inj needle  100µl saline |

*) 7 DNA plasmids **) 11 DNA plasmids.

Immunizations will be given as prime injections (HIV DNA) at weeks 0, 6 and 12 and as boost injections (MVA) at week 36 and week 60.

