**1.5 Endpoints**

*1.5.1 Primary:*

1. The safety of immunization will be assessed by clinical signs and standard biochemical and haematological laboratory tests where any worsening of the severity grade will be considered for causality with the vaccine.
2. The immunization will be evaluated by assessing local (pain, cutaneous reactions including indurations), general (fever, chills, headache, nausea, vomiting, malaise, myalgia) and other unsolicited adverse events within 28 days. Any grade III or IV event will be taken as an indication that the group of patients tolerate this schedule less well.

The primary safety parameters will be graded:

- Local adverse event Grade 3 or above (pain, cutaneous reactions including indurations).
- Systemic adverse event Grade 3 or above (temperature, chills, headache, nausea, vomiting, malaise, or myalgia).
- Other clinical or laboratory adverse events Grade 3 or above confirmed at examination or on repeat testing.

Any event attributable to vaccine leading to discontinuation of the immunisation regimen must be documented. Data on local and systemic events listed above will be solicited with specific questions or using a diary card for 7 days following each immunisation. Data on other clinical events and laboratory events will be collected with an open question at each visit and through routinely scheduled investigations.

*1.5.2 Secondary:*

A qualitative evaluation of cellular responses against peptides representing the different immunogens will be performed primarily by the ELISPOT technique. Additional testing will be performed by intracellular cytokine staining quantifying IFN-, IL-2, TNF- and MIP-1 production by CD4 and CD8 T cells, lymphoproliferation against inactivated HIV using fresh cells and multi-colour intracellular cytokine staining using cryopreserved cells for assessment of multiple T cell effector functions including immunophenotyping of responding cells. Testing for binding antibodies and, if binding antibodies are present, also neutralizing antibodies will be performed.

Group B1 will be compared with the id only group in the HIVIS study (Group A in HIVIS trial) for evaluation of the lower dose of HIV DNA (0.6 vs 1.0 mg).

Group B2 will be compared with Group B1 for evaluation of the lower dose of HIV DNA with and without electroporation.

Group B3 will be compared to the group B2 for the evaluation of HIV DNA as a boost compared to boosting with HIV MVA.

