**Week 60 (study visit 14)** the visit for the fifth and last injection of the study vaccine, is conducted by both the study nurse and the study doctor. Before injection the diaries over events after the last injection will be discussed with the study subjects and an abbreviate risk assessment and risk behaviour counselling will be performed. Enough time has to be planned for the visit so that all questions from the volunteers about the study can be answered or reflected upon. After blood donation the fifth injection is given and the visit is documented. Again volunteers will be observed for 30 minutes following injection and new diaries over events will be completed for 7 days. The visit should be recorded in the source documents including immunization, study number and any other information relevant to the study.

**Week 62 (study visit 15)** is conducted by the study nurse(s). The study form is filled in and blood donated according to flow chart. Abbreviated risk assessment and risk behaviour counselling are done.

**Week 64 (study visit 16)** is conducted by the study nurses(s)**.** Blood is donated for immunology.

**Week 72 (study visit 17)** is the final planned visit in the study. The visit is conducted by both the study nurse and the study doctor. Again the study doctor takes a complete medical history and performs a physical examination according to study visit 1. An extended risk assessment and risk behaviour counselling is performed and blood is donated according to flow chart. The visit should be recorded in the source documents including study number and any other information relevant to the study. All study subjects will be issued a card signed by the principal investigators (full names, tel. numbers and addresses) stating that the holder has participated as a volunteer in a HIV-1 immunization study and that the outcome of standard HIV diagnostic tests do not signify HIV-1 infection.

*2.4.1 Immunisations*

| **Group** | **N** | **Mode of Immunization**  **(w 0, 6 , 12)** | **Mode of delivery** | **Left arm (Ampoules 1**  **env)** | | **Right arm (Ampoules 2**  **gag, Rtmut)** | **Boost immunization**  **(w 36 and 60)** |
| --- | --- | --- | --- | --- | --- | --- | --- |
| B1 | 10 | Id  ZetaJet® | No electroporation | 1 inj 100µl  0,3 mg DNA* | 1 inj100µl  0,3 mg DNA* | | 1 im inj needle  MVA 108 pfu |
|  | 2 | Id  ZetaJet® | No electroporation | 1 inj 100µl saline | 1 inj 100µl saline | | 1 im inj needle  100µl saline |

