Study vaccine must not be administered to individuals with hypersensitivity to any component of the vaccine.

*2.4.3 Safety follow-up in the days following immunisation*

A diary card will be given, with instructions and a full verbal explanation, for participants to record local and systemic adverse events following immunisation, as well as medication taken. Volunteers will also be contacted the day following injection for a brief adverse reaction interview and subjects reporting any grade 2 or higher event will be prompted to a clinic visit. Should the volunteer be unreachable the designated contact will be contacted. In addition, volunteers will complete diaries over events for 7 days following each vaccination. Contact will be maintained by the clinical team, using a method chosen by the participant, as indicated by the evolution of adverse events, up to resolution of solicited local and systemic events. Additional visits may be recommended at the discretion of the clinical and principal investigators, if clinically indicated or in order to clarify observations.

All concomitant medication must be recorded in study form CRF with the reason for administration, the dosage regimen, the onset and end of treatment.

The following medications are prohibited while the subject is in the study:

- Immunomodulatory agents (i.e. immunoglobulin)

- Immunosuppressive agents (i.e., systemic steroids, chemotherapy)

- Live, attenuated vaccines. Other vaccines (subunit or killed) should be given at least two weeks before or two weeks after HIV immunization.

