**8.2 Analysis**

All safety end-points will be graded by the Clinical Investigator and reviewed by the Trial Management Group. Any queries about grade and relationship to study product that cannot be resolved will be referred to the Trial Coordinating Committee for a final decision.

The primary end-points:

1. The safety of immunization with the seven or eleven DNA plasmids carrying HIV-1 genes will be assessed by clinical signs and standard biochemical and haematological laboratory tests where any worsening of the severity grade will be considered for causality with the vaccine.
2. The immunization will be evaluated by assessing local (pain, cutaneous reactions including induration), general (fever, chills, headache, nausea, vomiting, malaise, myalgia) and other unsolicited adverse events within 7 and 28 days. Any grade 3 or 4 event will be taken as an indication that the arm is less tolerable.

The secondary endpoints

The secondary endpoint (immunogenicity) will primarily be assessed by IFN-γ ELISpot 2 weeks after the third DNA immunization, the fourth DNA or first MVA immunization and after the fifth DNA or second MVA immunization. Both number of responders and magnitude of responses will be tested for significance. Additional studies will be performed at other time points using other assays such as intracellular cytokine staining, lymphoproliferation assays, epitope mapping, binding (and if indicated) neutralization antibody assays.

Group B1 will be compared with the id only group in the HIVIS study (Group A in HIVIS trial) for evaluation of the lower dose of HIV DNA (0.6 vs 1.0 mg).

Group B2 will be compared with Group B1 for evaluation of the lower dose of HIV DNA with and without electroporation.

Group B3 will be compared to the group B2 for the evaluation of HIV DNA as a boost compared to boosting with HIV MVA.

Group B4 is will be compared to groups B1-B3 to show if priming with additional HIV-related plasmids will increase immunogenicity to any of the included antigens.

Figures/tables will be prepared including all participants’ results.

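### Routine medication questioning stops on the day of the last dose (4.3.7), so medication unrelated to an adverse event can go unrecorded from about day 8 onward, although 2.4.3 requires all of it to be recorded

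*Protocol*

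**What the plan says.** Protocol section 4.3.7 (Concomitant medication) sets the questioning rule: "Participants will be asked about medication taken at each visit up to and including week 60". It continues: "Thereafter, they will be asked about medication only in relation to adverse events reported".

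Section 2.4.3 (safety follow-up after immunisation) sets the recording rule, without an end date: "All concomitant medication must be recorded in study form CRF with the reason for administration". The same section prohibits immunomodulatory agents, immunosuppressive agents and live attenuated vaccines while the subject is in the study. It asks for two weeks between any subunit or killed vaccine and an HIV immunisation. It also issues a diary card, kept for 7 days after each vaccination, on which participants note medication as well as adverse events.

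On timing, section 1.2 places the boosts "as boost injections (MVA) at week 36 and week 60", and section 2.4 describes week 60 as "the visit for the fifth and last injection of the study vaccine". The safety endpoint in 1.5.1 covers "other unsolicited adverse events within 28 days"; section 8.2 gives the window as "other unsolicited adverse events within 7 and 28 days". The IFN-γ ELISpot is the main immunogenicity assay, and section 8.2 sets its timing as "2 weeks after the third DNA immunization, the fourth DNA or first MVA immunization and after the fifth DNA or second MVA immunization". Visits follow at weeks 62, 64 and 72.

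**The concern.** Asking at the week-60 visit covers medication only up to that visit. The first four doses are each followed by visits at which everyone is asked about medication; the fifth is not. Yet the period after the fifth dose contains the last of the three main ELISpot time points and the last 28-day safety window. The week-62 ELISpot follows the complete two-boost schedule, so it bears directly on secondary objective 3 (DNA with electroporation versus MVA as boost).

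The protocol itself treats immunosuppressants and other vaccines as relevant, because it restricts both. A site that follows 4.3.7 to the letter has no assured means of meeting the unqualified recording rule in 2.4.3 after week 60. Nor can it fully check that the prohibition, or the two-week spacing of other vaccines, was kept after the last dose. At stake are protocol deviations that nobody sees, and a safety and immunogenicity record that is less complete for one dose than for the other four.

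**Working it through.** No sample-size or error-rate figure is involved, and the plan states no figure to reproduce. The check is timeline arithmetic from the protocol's own visit weeks.

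**Inputs.** Doses at weeks 0, 6, 12, 36 and 60 (1.2). Visits at weeks 2, 8, 14, 16, 32, 38, 40, 62, 64 and 72, besides the dosing visits (2.4, 2.6). Safety window 28 days (1.5.1, 8.2). Main ELISpot 2 weeks after doses 3, 4 and 5 (8.2). Diary 7 days (2.4.3). Last routine medication question at week 60 (4.3.7).

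**Step 1: visit questioning by dose.** Window end = dose week + 28/7.

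| Dose | Week | Window ends | Non-dosing visits in window | Routine question there? |
|---|---|---|---|---|
| 1 | 0 | 4 | 2 | yes |
| 2 | 6 | 10 | 8 | yes |
| 3 | 12 | 16 | 14, 16 | yes |
| 4 | 36 | 40 | 38, 40 | yes |
| 5 | 60 | 64 | 62, 64 | no |

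The fifth dose is the only one of five with no routinely questioned visit in its window.

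**Step 2: ELISpot time points.** 12 + 2 = 14, 36 + 2 = 38 and 60 + 2 = 62. Only week 62, one of three, falls after the cut-off.

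**Step 3: allow for the diary.** The diary records medication through day 7 after the last dose. Uncovered by either diary or routine question:

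- within the 28-day window: 28 − 7 = 21 days (days 8–28);
- before the week-62 ELISpot: 14 − 7 = 7 days (days 8–14);
- to the final visit at week 72: (72 − 60) × 7 − 7 = 84 − 7 = 77 days.

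**Step 4: allow for the other routes.** Two further provisions narrow what can be missed on those days.

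- Medication linked to a reported adverse event is still asked about (4.3.7) and recorded with the event (4.1.4, 5.3).
- At week 72 the doctor repeats the complete history as at visit 1 (2.4). The visit-1 history documents ongoing medication (2.2). A drug still in use at week 72 should therefore appear.

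**Residual.** Medication or a vaccine that (a) is not linked to a reported adverse event, (b) is taken from about day 8 after the last dose, and (c) is finished before week 72. No provision in the protocol requires anyone to ask about this.

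**The case against.** The strongest reply is that most of the gap is closed elsewhere. The adverse event definition in 4.1 takes in intercurrent illness, injury and worsening of existing conditions. Events are sought by an open question at each visit (1.5.1), and those needing a doctor's visit or a prescribed drug are evaluated, with the medication recorded (4.1.4). Participants are healthy, and chronic illness needing continuous or frequent medical intervention is excluded. A systemic steroid course would normally be given for an illness that is itself an adverse event. This stands, and it narrows the residual mainly to elective vaccines, medication without an underlying event, and events that go unreported.

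It can also be said that 2.4.3 governs what is recorded in the days after immunisation, while 4.3.7 governs when staff ask, so the two can be read together. This softens the conflict but does not remove it. The days after week 60 are themselves days after an immunisation, and a duty to record everything is hard to meet when the question is not put.

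A reader might infer that the whole 28-day window after the last dose is unobserved. It is not: the diary covers the first 7 days, and event-linked medication is captured throughout. A reader might also take the 12 weeks after week 60, 12/72 = 16.7% of the study, as time with no medication data. That overstates the gap for the same reasons, and because ongoing medication is documented at week 72.

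Finally, a reader might suspect bias between arms. The documents do not support this: one rule applies to B1–B4 and to placebo, and the protocol specifies no analysis or exclusion based on concomitant medication.

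**Conclusion.** The point holds as a minor one. Section 4.3.7 ends active questioning on the day of the last dose, and this falls short of what 2.4.3 requires. After allowing for the diary, event-linked recording and the week-72 history, the gap is limited to completed medication or vaccines not linked to a reported event. It covers about days 8–28 of the last safety window (21 of 28 days) and the second of the two weeks before the week-62 ELISpot.

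The consequence is undetected deviations and uneven ascertainment between the fifth dose and the first four. The rule applies to all participants, planned at 48, but that is the number under the rule, not the number of missed exposures. The documents give no rate of such medication use, so no count can be estimated, and it may be very small.

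The conclusion assumes that the diary is completed and returned after the last dose as after the others. It also assumes that the week-72 history records ongoing medication, as at visit 1, without necessarily dating completed courses.

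**What to change.** Reconcile 4.3.7 with 2.4.3 by extending the routine medication question from week 60 to the existing visits at weeks 62, 64 and 72. Word the question so that it also covers vaccines received since the last visit, with dates. If the shorter period is preferred, week 64 is the minimum that covers both the last ELISpot and the last 28-day window; 2.4.3 would then need an explicit end date for recording. No treatment rule, sample or visit changes. The cost is one extra question at three visits that already take place, the last of which already includes a full history.

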### 5 Adverse events

Participants will be provided with a diary card and disposable thermometers at the immunizations. A study physician or nurse will be on call 24 hours a day for the duration of the study. All participants will be provided with a direct telephone number to call in case of any suspected adverse event.

**5.1 Definitions**

An adverse event is any adverse experience occurring during the course of the study including the screening period.

Criteria for grading clinical and laboratory events are listed in the appendix.

The severity of events reported on the adverse event form will be determined by the investigator, based on the Toxicity Grading Scale or if the event is not listed the event will be graded following these guidelines:

Mild (Grade 1): Transient or mild discomfort. No limitation in normal daily activity.

Moderate (Grade 2): Some limitation in normal daily activity.

Severe (Grade 3): Unable to perform normal daily activity.

Serious (Grade 4): Life threatening

Death (Grade 5)

A severe adverse event is one graded 3 or 4 by criteria in appendix. Some, but not all grade 3 and 4 adverse events will be “serious” by ICH GCP criteria below.

*5.1.1 Serious Adverse Events (SAEs)*

An adverse event is considered to be a “serious adverse event” by ICH Good Clinical Practice (ICH GCP) criteria if it results in the following:

- death,
- a threat to life,
- requires in-patient hospitalisation or prolongs existing hospitalisation (hospitalisation for elective treatment of a pre-existing condition is not included),
- results in persistent or significant disability or incapacity,
- is a congenital anomaly (i.e., the outcome of pregnancy involving a participant), or
- is any other important medical condition*.

*Examples of conditions regarded as “any other important medical condition” include allergic bronchospasm requiring intensive emergency treatment, seizures or blood dyscrasias which did not result in hospitalisation or development of drug dependency.

